### Ethics

Informed written consent will be taken from all participants and household heads. Consent will be also taken for ancillary studies and future use of specimens collected from study participants. This study protocol has been reviewed and approved by the icddr,b Ethical Review Committee. Approval will be taken for any addition or modification of the protocol from icddr,b Ethical Review Committee. If research staff members identify patients with hypertension or cases of hypertension during pregnancy, they will refer patients to the local government health facilities for further management. In addition, research staff will train pregnant women and family members to recognise the danger signs during pregnancy, and will also instruct them where to seek medical care if such danger signs appear. During monthly household visits, research staff will encourage pregnant women to attend prenatal visits. All data sets will be anonymous without the personal identifiers and participants’ privacy will be maintained during data storage, analysis and dissemination.

### Dissemination

Study findings will be shared with the DPHE, Department of Environment of the government of Bangladesh and other partner non-governmental organisations working in southwest coastal Bangladesh for access to safe drinking water. We will discuss the scope and limitations of the MAR system to address the demand of safe drinking water based on findings from this study. We will be submitting abstracts to international conferences for dissemination to the international audience working on safe water. We will develop manuscripts and submit to peer-reviewed journals to publish our research.

## Discussion

This will be the first study to assess the health impact of an environmental intervention to reduce groundwater salinity in southwest coastal Bangladesh. Our study has several strengths. The stepped-wedge trial ensures that we will have counterfactual data as well as gradual access to MAR water in all communities. In a stepped-wedge design, treatment effect of an intervention can be estimated from between and within-cluster comparisons as participants will act as their own control, compared with only between-cluster comparison in a parallel cluster-randomised design.^61^

We explored other study designs such as non-randomised study. As per suggestion of icddr,b’s Ethical Review Committee, we conducted a pilot study in four communities (two MAR communities and two non-MAR communities) from May to August 2016. Pilot study findings suggested that because of the heterogeneity in village-level hydrogeological conditions and in participation by community residents with different characteristics, non-randomised quasiexperimental studies would be expected to generate unequal distribution of confounders that would undermine scientific inference. The objective of the pilot study was to pretest our data collection instrument laboratory protocols prior commencement of the main study. We identified unequal distributions of several important observed confounders across the communities such as socioeconomic status, and household characteristics such as supply of electricity and ownership refrigerator. We identified that some covariates such as supply of electricity were perfectly predictive of communities receiving MAR interventions. We were unable to derive satisfactory matching of MAR intervention and control households after principal component analysis. The findings highlighted the importance of a randomised trial to evaluate the health effects of MAR systems since there are many observed and unobserved household and community-level and hydrogeological confounders that may influence blood pressure.

We also explored the possibilities of parallel group randomised trial but several programmatic issues barred us to implement a parallel group cluster-randomised trial. The implementers of MAR systems (Unicef Bangladesh and University of Dhaka) installed the 75 new sites in different stages and planned to allow communities to access these over three dry seasons. The implementers informed us that 20–25 MAR sites may be suitable for community access during our study period and they wanted to allow all communities to drink MAR water in the same season after satisfactory reduction in salinity. Therefore, a parallel group cluster-randomised trial was not suitable as we could not randomly select control sites and postpone the community to drink water for the dry season. We believe that the stepped-wedge trial design was appropriate to obtain counterfactual data as well as fulfilling the programmatic need.

We will use the same instruments for data collection and outcome measurements for all steps for exposed and unexposed communities, which will mitigate bias in data collection. Measurement of water source salinity and urinary sodium concentration will explain the biologically plausible effect of drinking MAR water on blood pressure. All outcomes planned to measure in the study are objective outcomes that will reduce the risk of reporting bias. Collection of detailed exposure and covariate data will help in determining a valid association between drinking MAR water and health benefits. We will have several outcome variables and biomarkers that will ensure a comprehensive health benefit evaluation of access to MAR water.

The study has several limitations. We will be unable to control salinity level of drinking water across the 16 MAR communities due to different hydrogeological conditions and volume of infiltrated water across the aquifers. Although the initial electrical conductivity of MAR water will be <2000 μS/cm, electrical conductivity is likely to vary across different MAR communities with the intensification of dry season. Therefore, MAR water salinity will differ across communities at a single point of time, and also for the same community at different points of time. This will result in different versions of exposures (ie, access to MAR water with different salinity levels) that may affect different responses for some participants depending on the version of exposure they will receive.^92 93^ To account this, we will specify the versions of exposure by measuring the salinity level of MAR water available in participants’ households and interpret the response as unit change of salinity at different MAR water salinity levels. As compliance of drinking MAR water may be different across communities despite active encouragement by promoters, one problem of the intention-to-treat analysis is that if the proportions of participants who will always drink MAR water are low compared with those who will not, the potentially greater effect of MAR intervention on blood pressure of fully participating individuals may be washed out by the smaller effect of those who will not comply. To account for this, as a secondary analysis, we will conduct ‘instrumental variable’ (IV) analyses by jointly running two regression models: a regression model for predicting urinary sodium excretion by drinking water salinity, and a regression model for blood pressure prediction given the urinary sodium excretion. The assumption of IV analyses is fulfilled in our context as the exogenous variable (IV) can only affect outcome variable (blood pressure) through influencing the endogenous variable (urinary sodium excretion).^94^ If MAR water has lower salinity than other water sources and if participants always drink MAR water, their urinary sodium excretion will be low compared with those who will not fully participate.

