**Methods and analysis:**

The study employs a stepped-wedge cluster-randomised controlled community trial design in 16 communities over five monthly visits. During each visit, we will collect data on participants’ source of drinking and cooking water and measure the salinity level and electrical conductivity of household stored water. At each visit, we will also measure the blood pressure of participants ≥20 years of age and pregnant women and collect urine samples for urinary sodium and protein measurements. We will use generalised linear mixed models to determine the association of access to MAR water on blood pressure of the participants.

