There are 37 million people living in the southwest coastal region and 20 million are currently affected by drinking water salinity.^39^ The estimated mean global sodium consumption is 3.95 g/day (range 2.2–5.5 g/day),^40^ but people in southwest coastal Bangladesh consume up to 16 g of sodium per day through drinking brackish groundwater.^41^ While MAR water can potentially reduce exposure to saline water, the health effects of providing access to MAR water have not been investigated. Characterising the health consequences of shifting from current drinking water supply to MAR water can assist decision makers to assess the value of scaling up MAR. Many water interventions, for example, failed to achieve health impact, because people do not use them. There is also considerable controversy on whether reducing sodium intake improves health.^42^ In addition, the MAR system will also alter the intake of other cations such as calcium and magnesium that may have health impact.^43–46^ Because the cost of these systems is high and their long-term feasibility an open question, clarifying the amount of health benefit, if any, is an important step that can help inform future efforts to provide water to communities faced with high levels of groundwater salinity. The human subject committees who reviewed the study appreciated the uncertainty in bringing solutions to scale in this setting and considered it appropriate to include health measurements of participating residents to objectively evaluate the potential impact.

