## Methods

### Study design

We will implement a stepped-wedge cluster-randomised controlled trial in 16 MAR communities. MAR system is a community-based intervention designed to supply low-salinity water for 60–70 households in a village or community. MAR intervention cannot be implemented and randomised at individual or household levels. Once a community will have access to MAR water, it is difficult to withhold the access of MAR water for some households. Therefore, we will conduct a cluster-randomised trial where each community will be considered as a cluster. The stepped-wedge design allows communities to gradually have access to MAR water; however, the point at which their access commences will be randomly assigned.^52^ In this way, each MAR site will contribute data for both the intervention and the control time periods. We will have five monthly steps in the stepped-wedge trial (figure 3). In the first step, none of the communities will have MAR water available for drinking and we will collect baseline information. During each subsequent month, four randomly selected communities will receive access to MAR water for drinking and cooking. In the last (fifth) monthly step, all the communities will have access to MAR drinking water.

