### Statistical methods

We will conduct an intention-to-treat analysis for the primary analysis. For the primary analysis, we will assess whether access to MAR water reduces the systolic blood pressure (continuous outcome) of the ≥20-year-old participants. Pregnant women will be included in the primary analysis because it is likely few pregnant women will be identified in the 16 communities and separate analysis of pregnant women will be underpowered. We will use generalised linear mixed models with appropriate links for the primary analysis considering random effects for community, households and participants, and fixed effects of steps or visits. We will adjust the effect of MAR systems on blood pressure for age, sex, weight and height, and personal and socioeconomic factors (table 2). We will inspect the missing data patterns and use multiple imputation with chained equations to jointly impute data on missing exposure and confounders to preserve an unbiased association estimate if the data are missing at random conditional on measured variables. We will also conduct subgroup analyses among the households that adhere with the MAR intervention and that exclusively use MAR water. If the trial demonstrates drinking MAR water has health effects, we will investigate the time required for health effects following receiving MAR intervention in secondary analysis.

**Table 2 T2:** Key variables to be used for assessing the health impact of access to MAR water

Outcomes	Exposures	Confounders	Covariates	Moderators
Systolic blood pressure	Access to MAR water	Sex	Age	Drinking/cooking from another water sources
Diastolic blood pressure	Drinking water salinity	Socioeconomic status	Weight	
Pulse pressure	Cooking water salinity	Education	Height	
Mean arterial pressure	Drinking water sources Cooking water sources		Waist circumference	
Urinary total protein Urinary sodium excretion			Mid-upper arm circumference	
			Adding table salt	
			Adding salt for cooking	
			Exercise level	
			Smoking status	
			Use of betel nuts	
			Stress	
			Diet	
			Urinary creatinine	

MAR, managed aquifer recharge.

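### The secondary instrumental-variable analysis uses non-randomised water salinity as its instrument and states as fact an assumption that the protocol does not support

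*Protocol article*

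**What the plan says.** In its limitations, the Discussion notes that low uptake could dilute the intention-to-treat effect, and offers a remedy: "To account for this, as a secondary analysis, we will conduct ‘instrumental variable’ (IV) analyses by jointly running two regression models". The first is "a regression model for predicting urinary sodium excretion by drinking water salinity"; the second is "a regression model for blood pressure prediction given the urinary sodium excretion". Salinity is therefore the instrument, urinary sodium the endogenous variable and blood pressure the outcome. The justification given is: "The assumption of IV analyses is fulfilled in our context as the exogenous variable (IV) can only affect outcome variable (blood pressure) through" urinary sodium excretion.

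Other sections bear on this:

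- Study design: what is randomised for each community is "the point at which their access commences will be randomly assigned".
- Abstract: at each visit staff will "measure the salinity level and electrical conductivity of household stored water". Exposure assessment adds a sample from the MAR outlet.
- Introduction (Background and rationale): "the MAR system will also alter the intake of other cations such as calcium and magnesium that may have health impact".
- Data collection methods: self-reported MAR use, exclusive or intermittent, is recorded for each household at follow-up visits.
- Statistical methods: the primary analysis is by intention to treat. A further plan is "subgroup analyses among the households that adhere with the MAR intervention and that exclusively use MAR water".

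**The concern.** A valid instrument must predict the endogenous variable, must be independent of unmeasured causes of the outcome, and must affect the outcome only through the endogenous variable (exclusion). The plan argues only the last and treats it as settled. The second is taken for granted by calling salinity exogenous.

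The Discussion gives confounding between households and communities as its reason for randomising. An analysis that replaces randomised access with measured salinity lets that confounding back in. It would do so in the analysis meant to show the effect in people who really drink the water, and the text assures the reader that it is valid.

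**Working it through.** The plan gives no figure for this analysis, so there is none to reproduce. The check compares its sections and then uses algebra to show what each departure does.

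**Independence of the instrument**

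1. Only the start of access is randomised (Study design; Randomisation and intervention delivery).
2. Salinity of stored water reflects the source a household uses. The strengths and limitations list expects compliance to differ by site and by socioeconomic status.
3. The Discussion says salinity cannot be controlled across the 16 communities, because hydrogeology and infiltrated volume differ.
4. The Discussion also says that observed and unobserved factors at household, community and aquifer level may influence blood pressure.
5. Table 2 lists drinking water salinity as an exposure, and socioeconomic status and education as confounders.

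Together these make salinity a variable that may share causes with blood pressure. They do not describe an exogenous one.

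**Exclusion**

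The Discussion allows one path only, through urinary sodium. The Introduction says MAR water changes intake of other cations with possible health impact. That is a second possible path.

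**What each departure does**

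Let Z be salinity, X urinary sodium, Y blood pressure and U a shared cause. Let β be the true effect of X on Y, π the slope of X on Z, δ a direct effect of Z on Y, and γ the effect of U on Y. After removing step and community effects, the IV ratio tends to

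β + δ/π + γ·Cov(Z,U) / (π·Var(Z)).

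All values below are assumed for illustration: β = 2.0 and π = 0.5. U is socioeconomic status (SD 1), with γ = −2 in the confounded case. Salinity falls by 0.3 per SD of U. Use after access is 50% on average and rises with U (probit slope 0.5). Use lowers salinity by 1, and residual salinity SD is 0.5. There are 16 communities, 60 people each and 5 steps.

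- Cov(use,U) = 0.5 × (0.5/√1.25) × 0.399 = 0.089, where the leading 0.5 is the share of community-visits with access.
- Cov(Z,U) = −(0.089 + 0.3) = −0.389.
- Var(use) = 0.25 × 0.075 + 0.5 × 0.25 = 0.144, where 0.075 is the variance of access left after step and community effects.
- Var(Z) = 0.144 + 0.09 + 2 × 0.3 × 0.089 + 0.25 = 0.537.
- Confounding term: (−2 × −0.389)/(0.5 × 0.537) = 2.9.

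| Scenario | Formula, salinity instrument | Simulated, salinity | Simulated, randomised access |
|---|---|---|---|
| No confounding, no direct path | 2.0 | 2.0 | 2.2 |
| Confounding, no adjustment for U | 2.0 + 2.9 = 4.9 | 4.8 | 1.9 |
| Direct path δ = −0.5 | 2.0 − 1.0 = 1.0 | 1.0 | 0.7 |
| Direct path δ = +0.5 | 2.0 + 1.0 = 3.0 | 3.1 | 3.1 |
| Direct path δ = +1.0 | 2.0 + 2.0 = 4.0 | 4.0 | 4.1 |

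Simulated values are medians of 200 replicates; departures from the formula are simulation noise. Randomised access repairs the confounding. It does not repair an exclusion failure while urinary sodium stays the endogenous variable, because δ/π is then unchanged. Both the instrument and the endogenous variable have to change.

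**The case against.** **The analysis is secondary.** This stands. The primary analysis compares randomised access by intention to treat and uses no salinity instrument. A reader might infer that the main result is at risk; nothing in the document supports that.

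**Planned adjustment may remove the bias.** This stands in part. Statistical methods plans adjustment for personal and socioeconomic factors. In the formula, perfect adjustment for U makes the confounding term zero. Another simulation with assumed coefficients and a true slope of 0.05 gave 0.085 with visit effects only and 0.050 once measured socioeconomic status was added. A reader might take the gap of 4.8 against 2.0 above as the expected error. It is not, because it leaves that adjustment out. However, the article does not say whether the IV models carry the adjustment, and it expects unobserved confounders, which no listed covariate is sure to capture.

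**The calcium and magnesium path is only possible.** This stands. The Introduction speaks of health impact in general and does not name blood pressure, so the violation is plausible and not proven. That is still enough against a claim that no other path exists.

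**Household salinity is an inference.** The IV sentence says only drinking water salinity, and the MAR outlet is sampled too. Stored household water is the natural reading for a model of individual sodium excretion. Outlet salinity would not be randomised either.

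**The adherent-household subgroup.** A reader might infer that it too is presented as causal. Statistical methods makes no such claim. Adherence is chosen after randomisation, so its results can only be descriptive.

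**Randomised access is imprecise.** This stands. In an illustration of 300 simulated trials with a true slope of 0.05, the access instrument had mean 0.051 and SD 0.058. Salinity, without socioeconomic adjustment, had mean 0.123 and SD 0.021. The SD ratio is 0.058/0.021 = 2.8. Root mean squared error is √(0.001² + 0.058²) = 0.058 against √(0.073² + 0.021²) = 0.076, a modest gain. Where adjustment removes all the confounding, salinity would be far more precise.

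**An article leaves detail to the full plan.** That does not apply. The article fixes the instrument, the endogenous variable and the justification, so this is a statement made and not a detail omitted.

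**Conclusion.** The point holds for the secondary IV analysis. Its instrument is not randomised, it depends on factors that the article says may be confounded with blood pressure, and the exclusion claim conflicts with the Introduction. The claim of a fulfilled assumption is unsupported as written.

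The size and direction of the bias cannot be derived from the document. They depend on how much confounding remains after adjustment and on any effect of calcium and magnesium on blood pressure, neither of which is given. The figures above show the mechanism under assumed values and do not estimate the error in this trial. The matter should be fixed before the analysis is run, but it is not critical to the trial's main conclusion.

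**What to change.** 1. Use the randomised access indicator (community by visit) as the instrument, with visit fixed effects and inference that accounts for clustering in 16 communities.
2. Make any MAR use the endogenous variable. Exclusive use alone will not do: intermittent use may also act, and access would then affect blood pressure outside the modelled path. With any use, changes in calcium and magnesium are part of the effect of use, so no sodium-only path is needed.
3. Replace the claim that the IV assumption holds with a stated assumption: access affects blood pressure only through use. Promotion begins at the start of the study in all communities, which helps, but the trial is unblinded.
4. Label the salinity, sodium and blood pressure model exploratory, adjust it for the Table 2 confounders, and cite the calcium and magnesium path as a limitation.
5. Keep the adherent-household subgroup as descriptive only.

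This costs analysis wording and no new data. The interval will be clearly wider than with salinity. The estimate is in essence the access effect divided by the access-related difference in use. For example, the planning difference of 3 mm Hg with an assumed use of 50% to 100% gives 6 to 3 mm Hg, and the standard error grows by about the same factor. It rescales the intention-to-treat result and cannot rescue a null one. Use is self-reported, and over-reporting would pull the estimate towards zero; stored-water conductivity can serve as a check.
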